## Abstract

**Background:**

Dysfunctional depressogenic cognitions are considered a key factor in the etiology and maintenance of depression. In cognitive behavioral therapy (CBT), the current gold-standard psychotherapeutic treatment for depression, cognitive restructuring techniques are employed to address dysfunctional cognitions. However, high drop-out and non-response rates suggest a need to boost the efficacy of CBT for depression. This might be achieved by enhancing the role of emotional and kinesthetic (i.e., body movement perception) features of interventions. Therefore, we aim to evaluate the efficacy of a cognitive restructuring task augmented with the performance of anti-depressive facial expressions in individuals with and without depression. Further, we aim to investigate to what extent kinesthetic markers are intrinsically associated with and, hence, allow for the detection of, depression.

**Methods:**

In a four-arm, parallel, single-blind, randomized controlled trial (RCT), we will randomize 128 individuals with depression and 128 matched controls without depression to one of four study conditions: (1) a cognitive reappraisal training (CR); (2) CR enhanced with instructions to display anti-depressive facial expressions (CR + AFE); (3) facial muscle training focusing on anti-depressive facial expressions (AFE); and (4) a sham control condition. One week after diagnostic assessment, a single intervention of 90–120-minute duration will be administered, with a subsequent follow-up two weeks later. Depressed mood will serve as primary outcome. Secondary outcomes will include current positive mood, symptoms of depression, current suicidality, dysfunctional attitudes, automatic thoughts, emotional state, kinesthesia (i.e., facial expression, facial muscle activity, body posture), psychophysiological measures (e.g., heart rate (variability), respiration rate (variability), verbal acoustics), as well as feasibility measures (i.e., treatment integrity, compliance, usability, acceptability). Outcomes will be analyzed with multiple methods, such as hierarchical and conventional linear models and machine learning.

**Discussion:**

If shown to be feasible and effective, the inclusion of kinesthesia into both psychotherapeutic diagnostics and interventions may be a pivotal step towards the more prompt, efficient, and targeted treatment of individuals with depression.

**Trial registration:**

The study was preregistered in the Open Science Framework on August 12, 2022 (https://osf.io/mswfg/) and retrospectively registered in the German Clinical Trials Register on November 25, 2024. Clinical Trial Number: DRKS00035577.

**Supplementary Information:**

The online version contains supplementary material available at 10.1186/s12888-024-06361-3.

## Background

Depression is a serious disease with symptoms such as persistent negative affect, anhedonia, and energy loss [1]. It is a common mental health problem with a global prevalence of 3.8% [2], a 50%-increased risk of mortality (for a meta-analysis, see [3]), and a high risk of chronicity [4]. Cognitive Behavioural Therapy (CBT) has proven effective in a vast number of studies [5], and is currently considered the gold-standard psychotherapeutic treatment for depression. However, consistently high attrition rates of up to 32% [6] and remission rates as low as 42% [7] suggest a dire need to further optimize the efficacy of CBT for depression. Moreover, since no more than 40% of individuals meeting criteria for depression receive minimally adequate evidence-based treatment [8], variations of CBT that can be easily disseminated are highly relevant for clinical practice.

One of the primary techniques in depression-focused CBT is cognitive restructuring, which aims to systematically modify cognitive appraisal processes that trigger depressed mood [9]. In CBT, therapists work with their patients to identify automatic, depressogenic thoughts (e.g., “I am a complete failure”) and replace them with more functional ones (e.g., “I can do this”). To better consolidate the novel functional thoughts, patients are often coached to verbalize them repeatedly. It is commonly assumed that this eventually leads to a change in the underlying depressogenic beliefs and to the novel functional thoughts becoming integrated into the patient’s automatic thoughts. Consequently, there is a positive effect on the patient’s mood and on other symptoms of depression [10, 11]. However, patients often respond to invitations to verbalize anti-depressive thoughts with comments such as, “I can say that, but I cannot feel it” or “I can say that, but I do not believe it,” and they experience the exercise as futile and not worthy of practicing further. This clinical experience aligns with the theoretical assumptions of the Interacting Cognitive Subsystems Theory (ICS; [12]), which distinguishes *intellectual* and *emotional* beliefs. According to the ICS, cognitive restructuring exercises modify depressogenic thoughts on an intellectual level, but not necessarily their “felt meaning.” ICS explains this phenomenon with different subsystems that interact to generate emotions. The theory posits that depressogenic schemas are activated whenever any input information is appraised as highly aversive, uncontrollable, and stable over time. Self-verbalized (and thereby perceived) thoughts are only one possible input, in addition to input from the visual, acoustic, and body-state subsystem (see Fig. 1). Depressogenic thoughts such as, “I am a complete failure” are generated by the so-called *propositional subsystem*, which creates propositional meaning reflecting individual interpretations of situations (e.g., as aversive, uncontrollable, and stable) based on past experiences. The activity in this subsystem is purely cognitive, resulting in *intellectual beliefs*. In contrast, *emotional beliefs* require input from the so-called *implicational subsystem*. This subsystem processes thoughts transferred from the propositional subsystem, but also visual, auditory, and body-state-related information conveying an implicational level of meaning. The latter is a key strength of the ICS, as it highlights how cognitive-emotional processes may be moderated by physical input from the body. Hence, the effects of thoughts on emotions are considered to be in part moderated by “emotional proprioception” [13]. For example, if individuals without depression occasionally think “I am a complete failure,” the propositional meaning is likely to cue depressed mood. However, if the individual experiences such thoughts while standing upright, perceiving sufficient body power, and maybe even smiling to themself for underperforming so terribly that it is almost entertaining, this emotional proprioception has previously been associated with *successfully* meeting significant challenges. Hence, it carries the implicational meaning that the situation might not be as aversive, uncontrollable, and stable as suggested by the cued negative thought, and protect from the activation of depressogenic schemas. Contrastingly, in individuals with depression, the same negative thought is likely to coincide with slumped body posture, frowning, and sagging corners of the mouth. Since this proprioception has repeatedly been associated with situations that were indeed highly aversive, uncontrollable, and stable over time, they validate the automatic thought. As a result, the implicational subsystem triggers the depressogenic schema, which in turn cues depressed mood. Regarding the development and maintenance of clinical depression, ICS claims that the depressogenic affect then likely prompts further depressogenic interpretations in the propositional subsystem while inducing bodily changes such as slumped body posture, frowning, sagged corners of the mouth, etc. Thus, the negatively biased interpretation and the bodily changes reinforce each other and trigger the depressogenic schema. This interaction between (a) the depressogenic interpretations in the propositional subsystem and (b) depression-related changes in body-state is called the *cognitive interlock of depression*.

**Fig. 1 Fig1:**
[figure not shown]
The generation of emotions in the Interacting Cognitive Subsystems Theory. Adapted from Affect, Cognition, and Change: Re-Modelling Depressive Thought (p. 59), by J. D. Teasdale and P. J. Barnard, 1993, Lawrence Erlbaum Associates. Copyright 1993 by Lawrence Erlbaum Associates Ltd. Adapted with permission

Drawing on these theoretical assumptions, we deduce that targeting emotional proprioception in addition to depressogenic thoughts, and thus, the *emotional* as well as the *intellectual belief*, might indeed further optimize the efficacy of cognitive interventions for depression. More specifically, anti-depressive kinesthesia, i.e., the subfacet of proprioception encompassing the awareness of body movement, appears to be particularly relevant, as it is a conscious act that the individual can purposefully engage in. Numerous empirical studies already provide evidence for a relationship between kinesthesia and emotional experience in general, and for depression in particular. For example, depression has consistently been linked to characteristic changes in gait and posture (for reviews, see, e.g., [14, 15]). Moreover, the experimental manipulation of gait and posture has been shown to lead to changes in emotional experience and depression-related cognitive processing (e.g., [16–24]). That said, facial expression could be even more critical in the context of inducing emotional beliefs since facial muscles are very sensitive and quick to respond to emotional experiences [25]. Indeed, the relationship between emotional experience and facial expression has been proven in multiple studies (for meta-analytic evidence, see [26]). More specifically, depression has been shown to be associated with characteristic facial expressions (e.g., [27, 28]) and, particularly, less facial expression of positive affect (as reviewed by [29]). In studies using electromyography (EMG) measures, individuals with depression display greater overall activity of the musculus corrugator supercilii (the so-called “grief muscle”) when confronted with affective pictures [30, 31] and during negative thinking [32]. Moreover, one study found an association between activation in the musculus corrugator supercilii and clinical improvement [33]. Consistently, induction of a sad facial expression or contraction of the musculus corrugator supercilii has been shown to be associated with a more negative interpretation of ambiguous stimuli (which is one of the cognitive biases found in depression) in a healthy sample [34]. Additionally, a recent meta-analysis of five randomized controlled trials (RCTs) showed that blocking the musculus corrugator supercilii via botulinum toxin injection can lead to a significant reduction of depressive symptoms in patients with depression compared to a placebo control group with a large effect size (*d* = 0.98; [35]).

Despite these encouraging findings, there are important gaps in the current literature. First, many studies focus on only one or a few kinesthetic parameter(s) (e.g., muscle activity), even though it can be assumed that the importance of the kinesthetic input is proportional to the number of kinesthetic parameters included in the analyses. Secondly, few studies focus on the interaction between kinesthesia and cognitive processes, although their interaction could be more important than each independent domain. Thirdly, current studies on treating depression by manipulating facial expressions use methods that are too invasive to be easily integrated into psychotherapeutic treatments (i.e., injection of botulinum toxin; [35]). Most importantly, no study has investigated the effects of augmenting cognitive interventions for depression via systematic kinesthetic manipulation, nor have researchers specifically studied the effects of experimentally manipulating the degree to which anti-depressive and depressogenic self-statements are deliberately accompanied by validating/invalidating kinesthesia. This is puzzling considering both clinical experience and theoretical frameworks (e.g., ICS Theory) clearly suggest this could be a promising approach to achieve more sustainable effects of cognitive interventions for depression.

In the present study, we aim to fill these gaps in the depression and CBT literature pertaining the role of kinesthetic input (facial expression) in the modification of depressive mood. The study, “EmpkinS-EKSpression” is part of the Collaborative Research Center (CRC) “Empatho-Kinaesthetic Sensor Technology – Sensor Techniques and Data Analysis Methods for Empatho-Kinaesthetic Modeling and Condition monitoring” (EmpkinS, CRC 1483, German Research Foundation). Its overarching goal is to derive information about clinically relevant states from minimally disturbing and non-invasive assessments of motion for research, diagnostic, and intervention purposes. Specifically, we intend to examine the extent to which the efficacy of an automated, smartphone-based cognitive reappraisal training (as a key cognitive restructuring technique) against depressed mood can be augmented by systematically pairing the vocalization of depressogenic self-statements with invalidating kinesthesia and the vocalization of anti-depressive self-statements with validating kinesthesia, respectively. We further aim to clarify the extent to which singular markers as well as the combined pattern of kinesthetic indicators are associated with depression and could, hence, be employed for the automated detection of depression.

## Methods

### Design

To examine the relevance of kinesthesia for treatment and diagnosis of depression, we aim to conduct a four-armed, parallel, single-blind RCT (see Fig. 2) in accordance with the CONSORT statement [36]. The study is preregistered in the Open Science Framework (https://osf.io/mswfg/). It will be carried out at the EmpkinS Lab of the Friedrich-Alexander-Universität Erlangen-Nürnberg, structured around a smartphone-based training. There will be three intervention conditions: (1) a cognitive reappraisal training (CR), (2) CR enhanced by instructions to deliberately display anti-depressive facial expressions (CR + AFE), and (3) facial muscle training focusing on anti-depressive facial expressions (AFE). The control condition (4) will receive a sham intervention. Participants will be randomly allocated to one of the four study conditions with a 1:1 allocation ratio. A block randomization with a randomly varying block size of four or eight will be performed following a randomization list generated using the blockrand-package in R Studio [37]. To control for confounding expectation effects, participants will be blinded regarding the study condition they are allocated to, but will be debriefed after study completion. Moreover, to avoid biased assessments, researchers conducting the follow-up assessment will also be blinded to participants’ group allocation.

**Fig. 2 Fig2:**
[figure not shown]
Study procedure. PHQ-8 = Patient Health Questionnaire-8; d = day; CR = cognitive reappraisal training; CR + AFE = cognitive reappraisal training enhanced by instructions to deliberately display anti-depressive facial expressions; AFE = facial muscle training focusing on anti-depressive facial expressions

### Participants

We will recruit two participant groups of equal size with differing diagnostic status: one group of individuals with clinically relevant depressive symptomatology and a control group of individuals without depression. The diagnostic groups will be matched according to gender and age. For the depression group, the main inclusion criterion is the presence of a diagnosis from the depressive spectrum according to ICD-10 criteria (F32 ‘depressive episode’, F33 ‘recurrent depressive disorder’, F34.1 ‘dysthymia’, and F43.20 & F43.21 ‘adjustment disorder with depressive symptoms’ [38]) according to the Structured Clinical Interview for DSM-5 Disorders - Clinician version (SCID-5-CV; German Version: [39]). The main inclusion criterion for the group without depression is a score < 10 on the Patient Health Questionnaire (PHQ)-8 [40]. Additional inclusion criteria for both groups include being ≥ 18 years, being able and willing to provide informed consent regarding study participation, and having sufficient German language skills (at least level B2 according to the Common European Framework of Reference for Languages). Exclusion criteria included the presence of any psychotic disorder (ICD-10 F2x), any substance dependence disorder other than nicotine (ICD-10 F1x.2), acute suicidality, any impairment of facial expression (e.g., due to facial paralysis or recent Botox treatment or autism spectrum disorder), and any type of dyschromatopsia. To ensure maximum external validity, we refrain from applying further potential exclusion criteria such as other clinical comorbidities, or concurrent pharmaco- or psychotherapy, but will record this information.

A power analysis was conducted with G*Power [41] to determine the necessary sample size for a 2-group-comparison of each of the intervention conditions (CR, CR + AFE, AFE) with the sham control condition. In absence of similar studies serving as reference for the determination of a critical effect, a team of three clinical experts agreed that an effect size of *d* = 0.5 would be therapeutically relevant. The power analysis yielded a necessary sample size of *n* = 32 for each of the four intervention conditions and two diagnostic groups based on a 2-sided analysis, a critical alpha-level of α = 0.05, and a power of β = 0.80. Hence, we will include *N* = 256 participants in total, composed in equal parts of participants with depression (*n* = 128) and without depression (*n* = 128).

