### Procedure

Recruitment will take place via newspaper and social media advertisements, mailing lists, and flyers on public bulletin boards. Furthermore, individuals with depression will be recruited via the outpatient clinic for psychotherapy of the Friedrich-Alexander-Universität Erlangen-Nürnberg, and by contacting psychiatric or psychosomatic clinics, counselling center, psychotherapists, and general practitioners in and around Erlangen via telephone or email.

The recruitment material will provide a QR code and link to the study website hosted by Unipark.com. Here, interested individuals will find extensive information on study aims and procedures (without jeopardizing blinding). Furthermore, they will be able to directly access the study screening questionnaire (T0) on demographic information, inclusion and exclusion criteria, and symptoms of depression. If eligible, participants will be invited to a first appointment in the laboratory for a diagnostic session (T1). During this session, after obtaining written informed consent, two diagnostic interviews (see Table 1) will be conducted by trained psychologists. All interviews will be video-recorded and 10% rated by a second expert to determine inter-rater reliability for diagnostic status. In case of ambiguity, the diagnostic status will be deliberated with experienced clinical psychologists. Moreover, participants will answer a set of questionnaires delivered on a computer tablet via Unipark.

**Table 1 Tab1:** *Overview of measures per Time Point*

Variable	Instrument	Time point					
		T0	T1	T2	Continuous^a^	T3	T4

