### Measures

#### Demographic and health-related information, screening, and diagnostics

Demographic and health-related variables assessed include age, date of birth, German language skills, nationality, gender, height, weight, academic degree, professional occupation, current academic field, relationship status, lifetime diagnosis of a psychiatric disorder, as well as history of and current psychotherapy and medication treatment.

The PHQ-8 will be used to screen for current depressive symptomatology during online screening (T0). The 8-item self-report measure assesses the frequency of eight of the nine criteria for depression according to the DSM-5 [1] during the previous two weeks on a four-point Likert-scale (0 = *not at all* to 3 = *nearly every day*). In contrast to the PHQ-9 [49], the PHQ-8 does not assess suicidality or self-injury. To ensure provision of adequate psychological support when necessary, we exclusively assessed suicidality/self-injury while face-to-face with participants. Previous studies showed comparable validity of the PHQ-8 and PHQ-9 in assessing depression [40, 50]. The items of the PHQ-8 can be summed up to a total score with a maximum of 24. A score ≥ 10 indicates clinically relevant depression [40].

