#### Preprocessing of kinesthesia and further psychophysiological data

Video data will be primarily processed with the FaceReader software [62], which offers an extensive array of visual features, including probabilities associated with basic emotions such as neutral, happy, sad, angry, surprised, scared, disgusted, and contempt - all discernible within each video frame. Additionally, it provides measurements of valence and arousal that are essential for understanding emotional states. Furthermore, it allows the extraction of so-called Facial Action Units (e.g., “Eyes Closed”, “Lip Stretcher”), offering insights into the intensity of expressions ranging between 0 and 1, and estimates head position and orientation in 3D (e.g., pitch, yaw, and roll rotation angles), complemented by 2D and 3D facial landmarks. The Facial Action Units and their variations provide detailed information on facial expressions and movements [63]. With regard to videos recorded with the Azure Kinect depth camera, we will extract depth information of body posture (i.e., the distance of each body part from the camera). Psychophysiological data, i.e., EMG, ECG, and respiration signals, will be preprocessed by extracting generic as well as specific features using various methods, particularly focusing on bio-signal feature extraction. Generic features of all psychophysiological data include mean, standard deviation, minimum, and maximum. Specific features of EMG signals include mean absolute value (MAV) and root mean square (RMS), specific features of ECG signals include heart rate and RR intervals, and specific features of respiration signals include respiration rate and respiration rate variability.

Cross-sectional comparisons between diagnostic groups (i.e., with vs. without depression) regarding baseline demographic, health-related, and clinical characteristics will be conducted using *t*-tests for continuous and Χ^2^-contingency tables for dichotomous variables, respectively.

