#### Automated detection of depression

Machine learning methods will be implemented to examine the automated discrimination between individuals with and without depression based on kinesthesia and other psychophysiological data (i.e., facial expression and body posture from video data, facial muscle activity from EMG, respiration, heart rate (variability), and verbal acoustics from audio recordings). Initially, only video data (facial expression/body posture) will be used. Subsequently, psychophysiological data and verbal acoustics data will supplement the video dataset, providing additional modalities for analysis. Ultimately, our long-term goal is to adopt a multi-modal machine learning approach to leverage all data modalities available to enhance the accuracy and robustness of depression identification.

For the classification task (i.e., discrimination between individuals with and without depression), different machine learning pipelines will be trained. This will consist of different steps, from pre-processing and normalization to feature selection and actual classification. After the machine learning process, we will use explainable artificial intelligence techniques to identify discriminative features and to interpret the output of the machine learning models. To split the data into training and test sets, we will employ a standard train-test split using the scikit-lear library train_test_split function with a fixed random seed and allocating 80% of the dataset for model training and reserving 20% for evaluation. This approach ensures reliable performance estimation while guarding against overfitting. The performance of the classification models will be evaluated using established metrics such as sensitivity (i.e., $$\:\frac{number\:of\:true\:positives}{number\:of\:true\:positives+number\:of\:false\:negatives})$$ and specificity (i.e., $$\:\frac{number\:of\:true\:negatives}{number\:of\:true\:negatives+number\:of\:false\:positives}$$), which are indicative of the classification task’s performance with a benchmark of 80%. Furthermore, we will test whether the balanced accuracy (i.e., $$\:\frac{sensitivity\:+\:specificity}{2}$$) will exceed the null distribution.

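### The detection aim speaks of markers intrinsic to depression, but the planned group comparisons and classifier cannot separate depression from its treatment

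*Protocol article*

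**What the plan says.** The Background paragraph of the abstract sets the second aim as finding "to what extent kinesthetic markers are intrinsically associated with and, hence, allow for the detection of, depression".

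The material for that aim is as follows.

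- **Matching.** Under Participants: "The diagnostic groups will be matched according to gender and age". No other matching factor is named.
- **Concurrent treatment.** Also under Participants, and for the sake of external validity: "we refrain from applying further potential exclusion criteria such as other clinical comorbidities, or concurrent pharmaco- or psychotherapy, but will record this information".
- **Recruitment.** Under Procedure, general advertising serves everyone, but in addition "individuals with depression will be recruited via the outpatient clinic for psychotherapy", and through psychiatric or psychosomatic clinics, counselling centres, psychotherapists and general practitioners.
- **Data held.** The demographic and health-related variables include "history of and current psychotherapy and medication treatment".
- **Stated use of those data.** The end of the preprocessing section plans cross-sectional comparisons of the diagnostic groups "regarding baseline demographic, health-related, and clinical characteristics will be conducted using" t-tests or contingency tables.
- **Detection.** "Machine learning methods will be implemented to examine the automated discrimination between individuals with and without depression based on kinesthesia" and other physiological signals (video, EMG, respiration, heart rate, voice). The data are split 80/20, sensitivity and specificity have a benchmark of 80%, and balanced accuracy is tested against a null distribution. The severity regression follows the same steps.

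**The concern.** A claim about depression itself needs a comparison in which the groups do not also differ in something that moves the sensor signals. Here depression status is observed, not assigned. One group is partly drawn from treatment settings, and drug treatment is allowed. If medication affects heart rate variability, facial movement, posture or voice, a classifier trained on these inputs can gain accuracy by recognising who is medicated. That medication has such effects is a clinical assumption; the article does not state it. The article does accept the general principle, because it excludes facial paralysis, recent Botox treatment and autism as causes of altered facial expression.

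The diagnostic-group hierarchical models, the classifier and the severity regression name no treatment variable as covariate, stratum or subset. Treatment is also absent from the limitations in the Discussion.

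At stake is how far the result carries over. The Discussion envisages automated diagnosis and monitoring. The article's own Background says that no more than 40% of people meeting criteria receive minimally adequate treatment. Accuracy that comes partly from reading treatment would not transfer to the rest.

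**Working it through.** The article gives no medication rate and no expected detector accuracy, so it has no figure of its own to reproduce on this point. The check asks how much accuracy medication alone could supply.

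**Inputs from the article.** There are 128 participants with and 128 without depression, and 20% are held out: 0.20 × 256 = 51.2, so 52 people if the split is by participant. An even split by diagnosis, 26 + 26, is assumed. The benchmark is 80% on both sensitivity and specificity.

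**Assumptions.** Let p1 be the medicated share of the depression group and p0 that of controls. The sensors are taken to read medication perfectly and to carry no other information. This gives an upper bound on what medication alone can do.

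**Formulas.** For a medication-only rule, sensitivity = p1, specificity = 1 − p0, and balanced accuracy = (p1 + 1 − p0)/2.

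- p1 = 0.30, p0 = 0.05: (0.30 + 0.95)/2 = 0.625
- p1 = 0.60, p0 = 0.05: (0.60 + 0.95)/2 = 0.775
- p1 = 0.20, p0 = 0.10: (0.20 + 0.90)/2 = 0.55

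**Null limit.** For an uninformative rule that flags a share q of the test set, the variance of balanced accuracy is about q(1 − q)/52. It is largest at q = 0.5, where the one-sided 5% limit is 0.5 + 1.645 × √(0.25/52) = 0.614.

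**Chance of success.** This was simulated with 20,000 draws on a 26 + 26 test set, using a one-sided permutation (Fisher) test at 0.05. Meeting 80% requires at least 21 of 26 correct in each class.

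| p1 | p0 | Balanced accuracy | Chance of exceeding the null | Chance of 80% on both |
|---|---|---|---|---|
| 0.20 | 0.10 | 0.550 | 0.17 | 0.00 |
| 0.30 | 0.10 | 0.600 | 0.46 | 0.00 |
| 0.30 | 0.05 | 0.625 | 0.72 | 0.00 |
| 0.40 | 0.05 | 0.675 | 0.91 | 0.00 |
| 0.50 | 0.05 | 0.725 | 0.98 | 0.00 |
| 0.60 | 0.05 | 0.775 | >0.99 | 0.02 |
| 0.80 | 0.05 | 0.875 | >0.99 | 0.58 |

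**Does the null test protect?** The article does not say how the null is built. If diagnosis labels are shuffled, shuffling also breaks the link between label and medication. Exceeding that null shows that the groups can be told apart, not why.

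**What an unmedicated subset would hold.** With p1 from 0.60 down to 0.30, 128 × 0.40 ≈ 51 to 128 × 0.70 ≈ 90 participants with depression are unmedicated. In the hold-out these are 26 × 0.40 ≈ 10 to 26 × 0.70 ≈ 18. At a sensitivity of 80%, the 95% half-width is 1.96 × √(0.16/10) ≈ 0.25 with 10 people and 1.96 × √(0.16/18) ≈ 0.18 with 18. If every participant had a cross-validated prediction, it would be roughly 1.96 × √(0.16/51) ≈ 0.11 to 1.96 × √(0.16/90) ≈ 0.08.

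**The case against.** A fair defence has five parts.

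**Medication is not ignored.** A reader might infer that it is recorded and then never used. The article does not support that. Medication is one of the health-related variables, and these are compared between the diagnostic groups at baseline, so an imbalance would be seen. This part stands. Seeing an imbalance does not remove it from the classifier, however, and the detection section does nothing further with it.

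**The performance benchmark is hard to reach on medication alone.** A reader might infer that a medication detector could pass as a good depression detector. At 30% to 60% medicated its sensitivity is only 30% to 60%, and the chance of 80% on both measures is 0.02 or less. This stands too. The exposed criterion is the weaker one, the test of balanced accuracy against the null. Below about 80% medicated, treatment would mainly inflate accuracy that has another source.

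**The imbalance is not documented.** A sharp difference in treatment is plausible but not stated. Advertising is also used, treatment is allowed in both groups, and participants with a current disorder are offered priority on the psychotherapy waitlist, which suggests that some are not yet treated. The size therefore stays an assumption.

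**The adverb appears in the abstract.** The aim at the end of the Background speaks only of association and detection, and the analysis section only of discrimination. That makes the wording easy to correct. It does not make the abstract's claim one that the design can support.

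**Details may lie in a fuller plan.** Covariate lists often do. But the article does fix the inputs, the split, the benchmark and the test, and that decision rule as stated cannot deliver the stated aim.

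**Conclusion.** The point holds in a limited form. The aim of intrinsic markers does not fit a non-randomised comparison that is matched on gender and age only, allows treatment, has clinical recruitment in one group, and leaves treatment out of the diagnostic-group models, the classifier and the severity regression. Balanced accuracy above the null could therefore partly reflect medication.

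The size depends on rates that the article does not give. At 30% to 60% versus 5%, medication alone yields balanced accuracy of 0.63 to 0.78 and exceeds the null with probability 0.72 or more. At 20% versus 10% the probability is 0.17. All these figures are upper bounds, because they assume perfect reading of medication by the sensors.

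A reader might also conclude that treated people should not have been admitted. That does not follow: the article gives a reason for admitting them, and the randomised comparisons and primary outcome are not touched by this point. The fault lies in the detection analysis and in one word of the aim.

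**What to change.** Add to the sections on efficacy and on automated detection:

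1. Code current psychotropic medication (yes/no) from the recorded medication data, before the detection analysis.
2. Report classifier sensitivity, with confidence intervals, separately for medicated and unmedicated participants with depression.
3. As a sensitivity analysis, repeat the classifier and the diagnostic-group contrast in the hierarchical models among participants without psychotropic medication. Preferably use cross-validated predictions, since a single 20% hold-out would contain only about 10 to 18 unmedicated participants with depression.
4. Unless the result is consistent in that subset, describe it as discrimination between partly treated patients and controls, not as an intrinsic marker.

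Medication-adjusted models can be added but are optional. Medication also tracks severity, so adjustment may remove real signal. At 5% only about 6 of 128 controls would be medicated (0.05 × 128 = 6.4), so the adjustment would rest almost wholly on contrasts within the depression group.

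The cost is some analysis text and reruns on data that are collected anyway. The drawback is low precision in the unmedicated subset, which should be read from its interval and not used as a pass/fail gate.
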